### Hypotheses of the study

Participants in the intervention group will have better improvement than the control group after the seven-session, 10-week modified MBCT intervention immediately after the intervention (T1) and/or at 6-month follow-up (T2) in terms of the following hypotheses: 1) significantly greater reduction of stress (primary outcome); and 2) significantly greater improvement in the secondary outcomes, namely depression, anxiety, resilience, burden, health-related quality of life, and the behavioral and psychological symptoms of the care recipient.

In addition, there are two hypotheses to facilitate the explanation of the positive changes in the modified MBCT group: 1) there will be significant positive correlations between the levels of mindfulness of the caregivers (total score of five facets of mindfulness) and the improvement in their stress, depression, anxiety, burden, resilience, health-related quality of life, and/or behavioral and psychological symptoms of the care recipient; and 2) increased use of all facets or individual facets of mindfulness skills of family caregivers will be significantly and positively correlated with the improvements in their psychological outcomes (stress, depression, anxiety, burden, resilience, and/or health-related quality of life).

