### Sample size

The sample size estimation was based on the primary outcome (stress). In the previous systematic review, the effect size of the MBCT for stress reduction was found to have Cohen’s *d* of 0.57 immediately after the intervention [15]. However, the intervention protocol is further modified and its duration is shortened in this proposed study. A conservative effect size Cohen’s *d* of 0.4 was adopted to detect the mean difference in stress reduction between the intervention and control groups. Based on the power analysis using the software G***Power 3.1 on repeated-measures analysis of variance (ANOVA), a sample size of 84 participants will be needed to achieve 80% power at a two-sided 5% significance level. According to the results of the feasibility study in Hong Kong, an attrition rate of 4% was found [16]. By adopting a more conservative estimation of the attrition rate of about 10%, the estimated sample size is at least 100 for this proposed study, 50 per group.

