### Data analysis plan

IBM SPSS 23.0 software will be used for the data analysis. The Kolmogorov–Simonov test will be used for checking normality. To ensure the similarity of the subjects in the two groups (modified MBCT and SIRE) at baseline, the demographics, adherence rate, frequency of mindfulness practice, and the outcome measurements will be compared by using a *t* test for continuous variables and a Chi-square test for categorical variables. Covariates will be controlled in the main analyses if a significant difference of variables is found at baseline. Both per-protocol (PP) and intention-to-treat (ITT) analyses will be performed. In the PP population, we will include the subjects who attend > 70% of the intervention sessions. A sensitivity test will be performed to compare the differences between the ITT and PP results. The aim of conducting both ITT and PP analyses is to uncover factors affecting the use and effectiveness of the modified MBCT, such as noncompliance and acceptability [48].

Descriptive statistic will be used to analyze the recruitment rate, attrition rate, duration, patterns, and consistency of the participants practicing mindfulness to indicate the acceptability of the MBCT. Mixed multivariate modeling (MANOVA) tests will be adopted to investigate the between-group effect (groups: modified MBCT and SIRE), the within-group effect (times: T0, T1, and T2), and the interaction time effect of group by time effect (group × time) on all of the outcome variables including PSS, HADS-A, CESD, ZBI, BRS, NPI-Q, and SF-12v2, and the process indicator (FFMQ). Correlation checking by Pearson’s product moment correlation of all the psychological outcomes including PSS, HADS-A, CESD, ZBI, BRS, NPI-Q, SF-12v2, and the process indicator (FFMQ) at baseline will be performed. If the correlation is too strong (Pearson’s *r* > 0.6), which may result in multicollinearity and violation of the assumption of mixed repeated MANOVA, then two-way repeated ANOVA and Bonferroni’s adjustments will be adopted to prevent a type I error [49]. Post-hoc pairwise comparisons using Tukey’s Honestly Significant Difference (HSD) will be performed to examine the significant difference in the outcomes.

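### The trial is sized on stress alone at two-sided 5%, but the analysis plan tests PSS jointly with the secondary outcomes or under a Bonferroni adjustment that the sample size did not allow for

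*Protocol article*

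**What the plan says.** **Hypotheses of the study** puts stress first and alone: "significantly greater reduction of stress (primary outcome"). The time of the effect is left open: "immediately after the intervention (T1) and/or at 6-month follow-up (T2").

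**Sample size** follows the same choice: "The sample size estimation was based on the primary outcome (stress"). A Cohen's d "of 0.4 was adopted to detect the mean difference in stress reduction between the intervention and control groups". With G*Power's repeated-measures ANOVA, "a sample size of 84 participants will be needed to achieve 80% power at a two-sided 5% significance level". Then: "By adopting a more conservative estimation of the attrition rate of about 10%, the estimated sample size is at least 100". No allowance for multiple outcomes is mentioned.

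**Data analysis plan** describes a mixed MANOVA for group, time and group by time "on all of the outcome variables including PSS, HADS-A, CESD, ZBI, BRS, NPI-Q, and SF-12v2, and the process indicator (FFMQ"). PSS is neither tested first nor set apart. The outcomes and FFMQ are to be correlated at baseline. If Pearson's r is above 0.6, "which may result in multicollinearity and violation of the assumption of mixed repeated MANOVA, then two-way repeated ANOVA and" Bonferroni adjustment replace the MANOVA. The plan does not say how many pairs, or which, must exceed 0.6, what the Bonferroni divisor is, or whether PSS is exempt. Tukey's HSD is named only for post-hoc pairwise comparisons.

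**Outcome measurement** says that FFMQ is collected in the intervention group only, and that its first measurement comes at the end of the third session, not at T0.

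**The concern.** The test that was powered is not the test that is planned. The sample size buys 80% power for one univariate test of stress at 5%. The analysis offers two other routes, and an observed correlation chooses between them.

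- **MANOVA route.** The null hypothesis is that no outcome differs. Rejecting it does not identify stress, and failing to reject it can hide a stress effect among outcomes that did not move.
- **Fallback route.** PSS gets its own ANOVA, but at a level reduced on account of the other outcomes. The primary outcome then pays for the secondaries, by an amount that cannot be read from the plan.

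At stake is whether the main conclusion has one determinate test at a known level. The MANOVA also cannot be run on the variables as listed, because one of them has no control-arm data.

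**Working it through.** **1. The plan's own figure.** Inputs from Sample size: d = 0.4, so f = d/2 = 0.2 for two groups; two-sided α = 0.05; power 80%; N = 84. The within-person correlation ρ, the number of measurements m and the effect tested (between groups or group by time) are not given. I use the noncentral F with

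- between groups: λ = f²·N·m / (1 + (m−1)ρ)
- group by time: λ = f²·N·m / (1 − ρ)

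The between-groups test with m = 3 and ρ = 0.12 gives λ = 0.04·84·3/1.24 = 8.13 and power 80.4%, so N = 84. The interaction gives N = 82 with m = 3 and ρ = 0, or with m = 2 and ρ = 0.2. So 84 is reachable at α = 0.05 with low correlations, but it cannot be confirmed. Attrition: 84/0.9 = 93.3, so 94. The planned 100 leaves 90 completers after 10% loss.

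**2. Effect of a Bonferroni divisor k.** Assume PSS has exactly 80% power at 84 completers. The standardised effect is 1.960 + 0.842 = 2.802, and it scales with √(n/84), which gives 2.900 at 90. Power = Φ(2.802·√(n/84) − z), with z the two-sided critical value at 0.05/k.

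| k | α | z | Power, 84 completers | Power, 90 completers |
|---|---|---|---|---|
| 1 | 0.05 | 1.960 | 80% | 83% |
| 2 | 0.025 | 2.241 | 71% | 74% |
| 7 | 0.00714 | 2.690 | 54% | 58% |
| 8 | 0.00625 | 2.734 | 53% | 57% |

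The divisors are assumptions: 7 is the number of outcomes, 8 adds FFMQ, and 2 is a mild case. Restoring 80% power would need about 102, 134 and 137 completers for k = 2, 7 and 8.

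**3. How far step 2 depends on the unstated design.** Power at N = 84 and f = 0.2:

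| Test | m | ρ | k = 1 | k = 7 | k = 8 |
|---|---|---|---|---|---|
| Between groups | 3 | 0.12 | 80% | 54% | 52% |
| Between groups | 3 | 0.5 | 60% | 31% | 29% |
| Group by time | 2 | 0.5 | 95% | 82% | 80% |
| Group by time | 3 | 0.5 | 98% | 92% | 91% |

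**4. MANOVA route.** As a simplified illustration, take a seven-variable Hotelling test with N = 84 (7 and 76 degrees of freedom), only PSS moving, and equal correlation r among outcomes. Set λ for PSS alone to 8.04, which gives 80% power for a single test on 1 and 82 degrees of freedom. The joint λ is 8.04·(1 + 5r)/((1 − r)(1 + 6r)). The multiplier is 1.00, 1.28 and 1.75 for r = 0, 0.3 and 0.5, and joint power is 46%, 58% and 75%. A rejection would still not point to PSS.

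**5. How likely the switch is.** The documents give no correlations. With seven outcomes, equal true correlations and N = 100, simulation puts the chance that at least one sample r exceeds 0.6 at 0.1% (true r 0.3), 8% (0.4), 61% (0.5) and 99% (0.6). Either route is possible.

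**6. FFMQ.** The Data analysis plan lists FFMQ among the variables of a comparison between groups over T0, T1 and T2, and in the baseline correlation check. Outcome measurement provides no control-arm FFMQ and no T0 value. At most seven variables can enter the between-group model, and FFMQ cannot be in a T0 correlation.

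**The case against.** The best defence is that the switch is written down in advance, has a numerical threshold and uses baseline data only, which carry no information on the treatment effect. That stands: large type I error inflation from the switch is not the problem. Nor is PSS always without a test of its own. The fallback gives it a separate ANOVA, and under the MANOVA post-hoc comparisons are foreseen. But the ANOVA is at a reduced, unstated level, and neither is designated as the primary test at 5%.

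Three stronger readings are tempting and are not supported.

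- A reader might infer that the trial is underpowered, at 54% or 53%. Those figures need an assumed divisor, exactly 80% power before adjustment, and 84 rather than 90 completers. If the test is the group-by-time interaction over three visits with a within-person correlation of 0.5, about 91–92% power survives a 7- or 8-fold adjustment.
- A reader might infer that a MANOVA would discard everyone with any missing score. The plan provides for LOCF or multiple imputation, so a complete-case analysis is not what it states.
- A reader might infer that the switch will almost certainly occur. No correlations are given, and the chance runs from near zero to near one over plausible values.

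It might also be said that such detail belongs in a statistical analysis plan. Here the article itself fixes the MANOVA, the variable list, the threshold and the Bonferroni step, and these conflict with its own sample-size basis.

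**Conclusion.** The point holds. The stated analysis does not deliver the test or the significance level on which 84/100 rests. On the MANOVA route stress is not tested separately at 5%; on the fallback route it is tested separately, but at an unstated reduced level. If PSS has exactly 80% power at 84 completers, a divisor of 2, 7 or 8 leaves about 71%, 54% or 53% (74%, 58% or 57% at 90). The true loss depends on the divisor and the within-person correlation, neither of which is given. What is firm is that the calculation made no allowance for the adjustment. Also firm, and free of any assumption, is that FFMQ cannot be in the between-group MANOVA or in a T0 correlation check.

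**What to change.** - Test PSS alone at two-sided 5%, as one prespecified group-by-time contrast at one named time point. If both times matter, test T1 and T2 in a stated order. Hypothesis 1 leaves the choice open, so naming PSS without a time would still not give a single test.
- Make this test independent of the r > 0.6 check, with no Bonferroni adjustment on account of the secondaries.
- Remove FFMQ from the between-group model and from the T0 correlation check. It can remain a within-arm process measure.
- Analyse the other six outcomes as secondary, with any multiplicity correction confined to them. A MANOVA of the outcomes may stay as a supportive secondary analysis.

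The cost is a change of wording. No data are added, and this point then gives no reason to alter 84/100. The price is that the joint multivariate test is no longer the main analysis.

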The Pearson’s correlation coefficient (*r*) (or Spearman’s correlation coefficient, as appropriate) will be adopted for the following variables to examine their correlations:The FFMQ total score as the independent variable and the outcome measurements including mean scores of stress, depression, burden, and anxiety as the dependent variables.The subscale (each facet) of the FFMQ score as the independent variable and the outcome measurements including mean scores of stress, depression, burden, and anxiety as the dependent variables.The duration of mindfulness practice as the independent variable and the level of mindfulness as the dependent variable.

The degree and pattern of missing data will be analyzed using SPSS Statistics Missing Values. If the missing value is a small amount (< 20%) and randomly distributed, the last observation carried forward (LOCF) method will be adopted to replace the missing data [50, 51]. However, if the missing values are not randomly distributed, multiple imputations will be adopted. This will create several different plausible imputed datasets and the results obtained from each of the sets will be appropriately combined [52].

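### The any-facet and and/or wording of the mindfulness hypotheses lets one of 24 unadjusted correlations in one arm support the mechanism claim, with roughly a 20% to 45% chance of a false positive in the hypothesised direction

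*Protocol article*

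**What the plan says.** **Hypotheses of the study.** Besides the efficacy hypotheses, the protocol states two that are meant to help explain any benefit in the MBCT group.

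- Hypothesis 1 concerns the FFMQ total score: "there will be significant positive correlations between the levels of mindfulness of the caregivers (total score of five facets of mindfulness"), set against improvement in seven outcomes joined by and/or.
- Hypothesis 2 concerns the facets. Its subject is "increased use of all facets or individual facets of mindfulness skills of family caregivers", and it predicts a significant correlation, in the positive direction, with gains on any of these: "stress, depression, anxiety, burden, resilience, and/or health-related quality of life".

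**Data analysis plan.** Pearson or Spearman correlations are planned for the FFMQ total and then for "The subscale (each facet) of the FFMQ score as the independent variable", each with "mean scores of stress, depression, burden, and anxiety as the dependent variables". A third item correlates practice duration with level of mindfulness. No time point, significance level, lead correlation or adjustment is given for these tests. Bonferroni appears in the same section ("adjustments will be adopted to prevent a type I error"), but only for the repeated-measures ANOVA used if the outcomes prove too strongly correlated for MANOVA.

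**Outcome measurement.** The FFMQ is collected in the intervention group only: at the end of session three, at T1 and at T2.

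**Limitations.** The protocol concedes possible bias because participants know their intervention. It says mindfulness will be measured to understand the mediating effect or active components.

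**The concern.** A hypothesis of significant correlation that can be met by any one facet, with any one outcome, gains a further chance of being met by luck with each pair examined. Here the wording of the hypotheses creates that error rate. A later analysis plan that added an adjustment would leave the published wording as it stands.

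What is at stake is the explanatory claim. Participants know their allocation and there is no FFMQ in the control arm, so the mechanism argument leans on associations within one arm of about 50 people. A chance facet-outcome pair in the expected direction would look like an active ingredient of the programme, and the hypothesis as written would let it be reported as confirmed.

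**Working it through.** The protocol states no test count or family-wise error for the correlations, so there is no figure of its own to reproduce.

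**1. Inputs**
- 5 facets plus 1 total score, and 4 outcomes (Data analysis plan).
- 50 people in the MBCT arm; 50 × 0.90 = 45 after the planned 10% attrition (Sample size).
- Two-sided 5% per correlation. This is an assumption: the protocol gives that level only for the sample size.
- Direction: both hypotheses require mindfulness to go with improvement, so only one sign can support them. At two-sided 5% that is 2.5% per test.

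**2. Count**
- Facets: 5 × 4 = 20. Total score: 1 × 4 = 4. Together 24.
- The practice-duration correlation would make 25, but it belongs to neither hypothesis and is left out.

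**3. Upper reference: independent tests, no true relation**

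Chance of at least one false positive = 1 − (1 − α)^k.

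| Tests | Either direction, α = 0.05 | Hypothesised direction, α = 0.025 |
|---|---|---|
| 4 (total score, hypothesis 1) | 1 − 0.95^4 = 18.5% | 1 − 0.975^4 = 9.6% |
| 20 (facets, hypothesis 2) | 1 − 0.95^20 = 64.2% | 1 − 0.975^20 = 39.7% |
| 24 (both) | 1 − 0.95^24 = 70.8% | 1 − 0.975^24 = 45.5% |

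**4. Allowing for dependence**

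The facets are likely to be correlated, so are the outcomes, and the total is the sum of the facets. The protocol gives none of these correlations, so a range is assumed. Simulation under no relation, n = 50, 24 Pearson tests:

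| Correlation among facets / among outcomes (assumed) | Either direction | Hypothesised direction |
|---|---|---|
| 0 / 0 | 67% | 42% |
| 0.2 / 0.3 | 62% | 35% |
| 0.3 / 0.5 | 55% | 29% |
| 0.4 / 0.6 | 49% | 25% |
| 0.5 / 0.7 | 43% | 22% |

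With n = 45 the results are nearly the same.

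**5. Expected number of false positives**
- 20 facet tests: 20 × 0.05 = 1.0 in either direction; 20 × 0.025 = 0.5 in the hypothesised direction.
- All 24: 24 × 0.05 = 1.2 and 24 × 0.025 = 0.6.

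**6. If both T1 and T2 were tested**

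The protocol does not say so. With an assumed correlation of 0.6 across time, the 48 tests give about 66% to 88% in either direction and 36% to 64% in the hypothesised direction, over correlations from 0.5 / 0.7 down to 0 / 0.

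**7. After adjustment**

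Bonferroni over 24 tests: 0.05 / 24 = 0.0021 per test, which holds the family-wise error at or below 5%. Holm's first step uses the same threshold.

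**The case against.** The best defence is that these hypotheses are explanatory. The protocol sets them apart from the efficacy hypotheses and calls the FFMQ a process indicator. It nowhere says that one significant pair confirms anything, and and/or could be a loose list of outcomes that might relate to mindfulness. A condensed article may also leave multiplicity for process correlations to an analysis plan that is not shown. The Bonferroni contrast is weak, since that adjustment belongs to a conditional fallback and is no general standard of this plan.

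Much of this stands. The absence of an adjustment alone would not be a finding, and the any-of rule is a reading of the wording. But it is the plain reading: hypothesis 2 predicts significance and expressly allows individual facets as an alternative to all of them.

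A reader might infer more than the documents support:

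- **That a false mechanism finding is more likely than not.** That needs results in the wrong direction to count, and both hypotheses exclude them. In the stated direction, 24 tests at one time point stay below 50% even if fully independent.
- **That several significant facets are expected by chance.** The expected number among the 20 facet tests is 1.0, or 0.5 in the stated direction.
- **That any facet can support both hypotheses.** That wording is in hypothesis 2 only; hypothesis 1 rests on the total score, with four planned tests.
- **That the tests are repeated over time.** Repeated FFMQ measurement makes this possible, but no time point is named for the correlations.
- **That these correlations are the protocol's answer to bias from unblinded participants.** The Limitations section says mindfulness will be measured for that purpose; it does not name these tests.

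**Conclusion.** The concern holds as a point about wording. As written, hypothesis 2 can be supported by one facet-outcome pair, and hypothesis 1 by one outcome. The plan supplies 24 correlations in a single arm, with no lead test.

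At one time point the chance of at least one false positive in the hypothesised direction is roughly 20% to 45%, against 2.5% for a single test in that direction. In either direction it is about 43% to 71%, against 5%. These figures rest on a two-sided 5% level per test, on no true relation between mindfulness and any outcome, and on the assumed ranges of correlation. Testing at both T1 and T2, if done, would raise them.

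The consequence is confined to the explanation of how the programme works. The comparison of groups on stress does not depend on it.

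**What to change.** 1. Name one confirmatory correlation in advance, with its time point: for example FFMQ total with PSS improvement at T1.
2. Remove the alternative of individual facets, and the and/or across outcomes, from the wording that defines success in the two hypotheses.
3. Report all other facet and outcome correlations as exploratory estimates with 95% intervals and no claim of significance. If formal claims on them are wanted, apply Holm across the 24.

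This changes wording only; no data collection or sample size is affected. The cost is that fewer facet results can be called significant: under Holm, the smallest p-value of the 24 must be at or below about 0.002.

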**Methods:**

A prospective, single-blind, parallel-group, randomized controlled trial will be adopted. A convenience sample of 100 community-dwelling family caregivers of PWD will be randomized to either the modified MBCT or the control groups. The modified MBCT group will receive a 10-week, seven-session, group-based modified MBCT whereas the control group will receive a social interaction and routine education (SIRE) on dementia care program at a frequency and timing similar to those in the intervention group. The primary outcomes (stress) and secondary outcomes (depression, anxiety, burden, health-related quality of life, and the behavioral and psychological symptoms of the care recipient) will be measured immediately post-intervention (T1) and at 6-month follow-up (T2), which will be compared with the baseline (T0).

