In the past few decades, mindfulness-based intervention (MBI) has been found to be effective at improving a few of the main psychological symptoms, including anxiety, depression, psychotic symptoms, and stress [7–12]. The most commonly used MBI is the Mindfulness-Based Stress Reduction (MBSR) program [13] and mindfulness-based cognitive therapy (MBCT) [14]. The MBSR was developed by Jon Kabat-Zinn in 1970 at the Stress Reduction Clinic at the University of Massachusetts Medical School and was primarily designed for patients with chronic pain. It is a group-based and multi-component intervention involving a wide range of activities, including sitting meditation, mindful walking, mindful eating, body scanning, group sharing, home practice, and psychoeducation on stress and psychological health. Based on the MBSR, Segal et al. [14] developed the MBCT to prevent a lapse into depression in people with a major depressive disorder. Similar to the MBSR, the program consists of eight 2-h weekly sessions with a 1-day retreat. MBCT adopted the principles of MBSR and integrated cognitive-behavioral techniques that explore more on negative thinking and its impacts on the well-being of participants [14]. Compared with MBSR, MBCT involves imagining particular scenarios and asks the participants to notice what thoughts appear. At the same time, the participants are taught to focus less on reacting to incoming stimuli (stressors) and instead on accepting and observing the stimuli without judgment.

A systematic review was conducted by us which included five experimental studies to investigate the effect of MBI (including MBCT and MBSR) on stress reduction in the family caregivers of PWD [15]. The result showed that the stress levels dropped significantly after an 8-week MBI in the family caregivers of PWD with a moderate aggregated effect size of 0.57 (95% confidence interval (CI) 0.23–0.92, overall effect *Z* = 3.25; *p* = 0.001). While an immediate effect of MBI was seen, the long-term effect (i.e., 6 months after the intervention) was unclear. Furthermore, a limited number of clinical trials and several limitations (such as poor study design, small sample size, lack of information on the adherence rate when practicing mindfulness, and a high attrition rate) were also identified in this review. This signifies that more studies are still required to examine the effects of MBI for family caregivers of PWD.

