## Conclusion

According to the recent systematic review, only a few clinical trials have reported a preliminary and short effect of mindfulness in the family caregivers of PWD. To meet the needs for the family caregivers of PWD, this proposed study has collected feedback from family caregivers of PWD and addressed the limitations (i.e., a low adherence rate) from previous studies by modifying the original MBCT protocol. The modified MBCT protocol aims to facilitate and support the family caregivers by cultivating a mindful attitude, empowering themselves to manage their stress, and promoting their resilience. The stress of family caregivers can last a long time, and hence examining the sustainable effects of the modified MBCT (i.e., a 6-month follow-up) is important. This study will also collect other important information on the intervention, including the participants’ adherence to mindfulness practices, level of mindfulness, and qualitative data for better understanding the active ingredients of the modified MBCT. The findings from this proposed randomized controlled trial could provide scientific evidence for the effectiveness of the modified MBCT for family caregivers of PWD. If significant benefits are found, the modified MBCT can be used as a standard supportive intervention for the family caregivers of PWD.

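### Filling small, randomly distributed gaps by last observation carried forward can bias the 6-month stress effect, where a mixed model or multiple imputation would not

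*Protocol article*

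**What the plan says.** The protocol article, Data analysis plan, sets a two-branch rule, chosen after the amount and pattern of missing data have been examined in SPSS.

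- Branch 1, the condition: "If the missing value is a small amount (< 20%) and randomly distributed". The method: "the last observation carried forward (LOCF) method will be adopted to replace the missing data".
- Branch 2: "if the missing values are not randomly distributed, multiple imputations will be adopted". It is described only in general terms: "This will create several different plausible imputed datasets and the results obtained from each of the sets will be appropriately combined".

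Randomly distributed missingness of 20% or more falls under neither branch. The only sensitivity comparison named in that section is intention-to-treat against per-protocol, which does not vary the missing-data assumption.

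Outcomes are taken at baseline (T0), "immediately post-intervention (T1) and at 6-month follow-up (T2"). Data collection procedure places T1 no later than a week after the programme ends. The primary hypothesis covers stress "immediately after the intervention (T1) and/or at 6-month follow-up (T2"). Background says that "the long-term effect (i.e., 6 months after the intervention) was unclear", and the Conclusion adds: "hence examining the sustainable effects of the modified MBCT (i.e., a 6-month follow-up) is important".

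**The concern.** LOCF assumes that a participant's score does not move after the last visit attended. For someone lost between T1 and T2, the 6-month value becomes the score recorded just after the programme. Whether that score holds for 6 months is what T2 is meant to find out, so for these participants the method presupposes the answer.

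The branch that uses LOCF is also where it is least needed. If values are missing at random, a likelihood-based mixed model or multiple imputation gives a valid estimate. LOCF does not, even when values are missing completely at random, unless the effect is constant after the last visit.

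At stake is the claim of a lasting stress reduction. If the benefit fades, part of it would be reported as sustained. If dropout happens during the programme instead, real effects at T1 and T2 would be diluted.

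**Working it through.** **Inputs from the protocol article**
- Planning effect, Cohen's d = 0.4 (Sample size). Used here as the T1 effect, δ1.
- Planned attrition about 10%; feasibility attrition 4% (Sample size).
- LOCF applies below 20% missing (Data analysis plan).
- 50 per arm (Sample size).

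**Assumptions, not in the documents**
- True T2 effect δ2: shown for 0, 0.1, 0.2 and 0.4 SD.
- Missing completely at random, which is the most favourable case for LOCF.

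Effects are in SD units, with a positive value meaning benefit of MBCT.

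**Which branch applies.** Both 4% and 10% lie below 20%, so LOCF is used unless the pattern check points to non-random missingness.

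**Dropout after T1, same fraction p in each arm.** A fraction p of T2 values is replaced by T1 values:

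expected LOCF estimate at T2 = (1 − p)·δ2 + p·δ1, so bias = p·(δ1 − δ2).

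| True δ2 | p = 4% | p = 10% | p = 20% (limit of branch) |
|---|---|---|---|
| 0 | 0.016 | 0.04 | 0.08 |
| 0.1 | 0.112 | 0.13 | 0.16 |
| 0.2 | 0.208 | 0.22 | 0.24 |
| 0.4 | 0.40 | 0.40 | 0.40 |

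For δ2 = 0.1 and p = 10%: 0.9 × 0.1 + 0.1 × 0.4 = 0.13, a bias of 0.03. For δ2 = 0: 0.1 × 0.4 = 0.04. At 20% the two biases are 0.06 and 0.08. When δ2 = δ1 the bias is zero.

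**Dropout before T1.** T0 is carried to both visits, and the expected T0 difference between randomised arms is zero. The estimates become (1 − p)·δ1 at T1 and (1 − p)·δ2 at T2. With p = 10% and δ2 = 0.1, that is 0.36 instead of 0.40 at T1, and 0.09 instead of 0.10 at T2.

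**Both kinds of dropout.** With p1 lost before T1 and p2 lost after it, bias at T2 = p2·(δ1 − δ2) − p1·δ2. Splitting 10% evenly with δ2 = 0.1 gives 0.05 × 0.3 − 0.05 × 0.1 = 0.01. With δ2 = 0.2 the two terms cancel.

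**Unequal dropout.** The bias is p × (mean T1 − mean T2) in the MBCT arm minus the same product in the control arm, so changes within each arm matter as well.

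**Simulation check.** 8,000 runs, 50 per arm, T1 observed for everyone. Assumed: correlation 0.6 between visits, control mean 0.1 SD below baseline at T1 and back to baseline at T2, true T2 effect zero.

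| Missing T2 (MBCT / control) | LOCF estimate | Rejection at nominal 5% |
|---|---|---|
| 4% / 4% | 0.014 | 5.1% |
| 10% / 10% | 0.039 | 5.4% |
| 20% / 20% | 0.081 | 6.9% |
| 20% / 5% | 0.093 | 7.8% |
| 5% / 20% | 0.002 | 4.9% |

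Observed-case estimates from the same data were within 0.005 of the truth. With a true T2 effect of 0.2 and 5% / 20% missing, the formula gives a bias of 0.005 against MBCT, so the direction can reverse.

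**Scale.** With 50 per arm the standard error of a difference in means is √(2/50) = 0.20 SD. A bias of 0.04 is a fifth of that.

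**The case against.** The strongest defence is size. LOCF is confined to less than 20% missing, and at the planned attrition the bias is at most about 0.04 SD under the assumptions above, with a false-positive rate of 5.4%. It disappears if the effect is maintained and dropout follows T1 equally in both arms. All of this stands, and it limits the weight of the point. It does not make LOCF a sound choice, because the bias depends on the unknown that T2 is meant to measure.

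A reader might infer three stronger things that the documents do not support.

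- *The rule is fully inverted, so the multiple-imputation branch is wrong too.* The article does not speak of missing at random or missing not at random. It judges the pattern of observed missingness, which can reveal a departure from completely random missingness but cannot separate the other two mechanisms. The natural reading of branch 2 is therefore missingness that is not completely random. This includes missing at random, where multiple imputation is appropriate.
- *LOCF will inflate the 6-month benefit.* It may, but the bias is conditional. Dropout during the programme pulls the estimate toward zero, and unequal dropout or a growing effect can reverse the sign. Large percentage overstatements come from dividing by a small assumed δ2.
- *Standard errors will be too small.* LOCF does treat filled values as observed, but this is not shown to matter for the T2 group comparison. In a simulation with 50 per arm and an assumed correlation of 0.6, the model and empirical standard errors were 0.200 and 0.201 at 10% missing, and both 0.201 at 19%.

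Details such as imputation predictors or a delta-adjusted analysis are commonly left to an analysis plan. Their absence from the article is no fault.

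**Conclusion.** The point holds for the LOCF branch. The article commits to LOCF under the conditions most likely to arise, and nothing elsewhere in it withdraws that choice. The resulting T2 bias is modest at planned attrition and roughly double near the 20% limit. Those sizes rest on δ1 = 0.4 from the sample-size section, on assumed values of δ2, and on equal, completely random dropout after T1. Under other dropout patterns the bias can be zero or point toward no effect. The multiple-imputation branch is defensible as most naturally read. This is a change that should be made, because better methods are available for the same data. It does not threaten the trial's validity.

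**What to change.** Remove the LOCF branch and the switch based on the missing-data pattern. A method valid under missing at random is also valid under completely random missingness, so nothing is gained by switching. With only about 10 dropouts expected among 100 participants, a pattern check could rarely tell the cases apart.

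Instead, analyse all randomised participants with a likelihood-based mixed model on all available T0, T1 and T2 data, or with multiple imputation, whatever fraction is missing. This also closes the gap for random missingness of 20% or more. LOCF can stay at most as a sensitivity analysis.

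Optionally, if non-random dropout is suspected, add a delta-adjusted sensitivity analysis for PSS at T2, since standard multiple imputation assumes missing at random.

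The cost is a change of analysis wording and, if wanted, one extra analysis. No further data are needed.
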